## Abstract

**Background:**

ICU stay is often associated with negative experiences for the individual patient. Many patients are disabled and their communication is restricted during the ICU stay. Specific information on procedures, sensations and coping behavior are thought to reduce anxiety on the ICU. Until now information programs to reduce anxiety were mainly delivered preoperatively, completely neglecting informational needs of non-elective ICU patients.

**Methods:**

The trial is designed as a prospective multicenter randomized controlled trial in the cities of Marburg, Halle and Stuttgart. Elective and non-elective ICU patients will be included. The trial includes an intervention and a control group on the ICU. The control group receives a trivial conversation without any ICU-specific information. The intervention group receives an information program with specific procedural, sensory and coping information about their ICU stay. Both conversations take place in the ICU and are planned to take about 10 minutes.

**Discussion:**

In contrast to former trials on information programs on the ICU-stay our intervention will take place in the ICU itself. This approach will ensure to compensate for memory effects due to anesthesia or preoperative stress. Further the results will be applicable to non-elective ICU-patients.

**Trial Registration:**

ClinicalTrials NCT00764933

## Background

ICU stay for ventilated patients is associated with severe impairments and limitations of communication. Additionally, these patients are restricted regarding their activities and ability to participate. These restrictions are mainly due to structural and procedural necessities including therapeutic interventions. The patients are not only handicapped by their vocal restraints, but also by the unknown and unfamiliar situation in the ICU. Nonetheless, ventilated patients are able to actively communicate with their environment. Research shows that nurse-initiated nurse-patient communication is lacking in this phase of ventilation [1]. If the nurses are interacting with the patient, the interaction is nonverbal and rather instrumental. With the patient getting more and more awake and able to respond, nurse-initiated communication increases [1].

Research into the communication behavior in intensive care units, not limited to ventilated patients, showed interactions and interaction conditions which had predominantly been perceived as problematic by patients [2-10]. ICU patients often experience these ineffective communication situations with feelings of anxiety, insecurity but also irritation. Particularly ventilated patients evaluate the communication during their ventilation as non-successful [3,10,11]. In this context, Alasad and Ahmad [2] found that communication with patients in ICUs is not continuous and strongly depends on the patient's condition. Intensive care nurses found work with awakened patients being able to communicate verbally as more exhausting, as compared to still unconscious patients. Here, communication was also not perceived as a possibility of informing and supporting the patient.

Similarly, Scheer [12] observed that the nursing staff in ICUs often feels overstrained and tends to withdraw from the patients' bedsides. Similar results were obtained by means of a video analysis which investigated the communication and interaction between ventilated patients and nursing staff in an ICU [1]. This analysis focused on the patient's remaining possibilities of expression in the different treatment stages taking into account also aspects of initiative and responsive communication. As a result, lessons in specific communicative abilities for nursing staff in intensive care were proposed, as the staff had acted upon "normal" social communication patterns and had not sufficiently observed the particularities of the setting [1].

The high priority of successful communication with communicatively challenged patients, however, is also appreciated by the ICU nursing staff [11,13]. In their qualitative study, Usher and Monkley [13] investigated the point of view of nursing staff on successful and effective communication in an ICU and were able to identify three main issues: "perception of caregivers", "presence" and "strain relief" - whereas the category "strain relief" is mainly made up of the situational information of the patient. This perception of successful conscious communication is opposed by the notion that communication is always something random and natural [13]. Against the background and as a consequence of Liedtkes [1] results, a concrete and conscious communication intervention for the information of the ICU patient and with "strain relief" in mind would be necessary.

Only one randomized controlled study (RCT), could be found which deals with a information intervention in the ICU [14]. For their research approach in cardiac surgery patients, Hwang et al. [14] chose a recorded tape information from the attending physician which was played to the patients after recovering from anesthesia. The contents of the 6 to 8 minute recordings included the course as well as the result of the operation and further treatment plans. The intervention group showed significantly superior values regarding anxiety, tension, depression and pain perception compared to the control group. The results of this study suggest the effectiveness of postoperative situational information intervention for a positive influence on psychological parameters. Therefore a nursing care information program comparable to and modeled on the brief medical information is to be tested in the planned trial with ICU patients.

### Trial objective

The aim of the project is to evaluate the effectiveness of a structured information program for patients who are staying in an ICU and thus having an associated induced communication restriction. In line with notions of control theory and nursing theory, the communication of knowledge is regarded as a means to enhance patients' capacity to understand, classify and predict the many unfamiliar events related to the ICU stay [15-17]. In this way it is not only possible to achieve an improvement of the difficult communication situation, but a cognitive reframing of the anxiety provoking ICU-stay. This can result in an increased perceived locus of control and eventually in stress reduction.

The key study hypothesis is:

An information program in the initial stage of treatment in an ICU alleviates unpleasant experiences related to the ICU stay and thus contributes to an improvement of the patient's situation and of particular aspects of quality of life, i.e. in relieving anxiety.

Besides this main point there are also other, secondary hypotheses particularly assuming effects on individual quality of life 3 months after discharge.

## Methods

The trial is designed as a multicenter trial with concealed random allocation and central data monitoring (coordinating center: Marburg; 3 study centers). The multicenter design was chosen to increase the generalizability of the study results. Within the framework of the Medical Research Council [18,19] this corresponds to the main phase of the evaluation of complex interventions, because the trial is designed as an extension to a previous study of our working group [20,21]. Study methods include the randomization on the patient level and the delivery of the intervention by members of the study group. Potential contaminations of the intervention and control group will be avoided by restricting recruitment to one patient per room on the ICU at the same time.

### Inclusion and exclusion criteria

Cardiac surgery, general surgery and internist patients with scheduled and unscheduled ICU stay (including High Dependency Units) will be eligible for inclusion in this trial. Exclusion criteria, besides a refusal to take part in the trial, are: no opportunity to fill in the mailed follow-up questionnaire, impaired cognitive ability and/or ability of judgment, language problems, accommodation in one room with another study patient, or age under 18 years.

### Recruitment of participants

Information and instruction of the patients is done personally and in written form by executive persons, the consent is obtained in writing (see Figure 1).

**Figure 1 F1:**
[figure not shown]
**Obtaining patient consent**. Patient information leaflet and patient consent form (translated version).

All patients who are to be admitted electively to the ICU will be informed about the possibility of taking part in the trial before the transfer to the ICU or before the surgery and their informed consent will be obtained. This applies to the major part of cardiac surgery patients as well as to a minor part of the general surgery patients. All other patients, particularly those of internal medicine and trauma surgery, will be informed about the trial in the early stages of their intensive care stay and will be asked to take part. In case custodians are appointed, they will be informed about the possibility of taking part in the trial and will be asked for a participation of their charge in the trial.

### Randomization

The group allocation is done via concealed randomization (concealed allocation) on the patient level, stratified by center and unit into 2 study groups:

▪ structured information at the beginning of the ICU stay (*Intervention group*) or

▪ sham comparator, unspecific conversation (*Control group*).

The randomization list will be computer-generated before the start of the trial (Institute of Medical Epidemiology, Biostatistics, and Informatics, Halle/Saale). Concealed randomization will be realized by using opaque, consecutively numbered envelopes after the inclusion of the study patients.

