### Blinding

Patients and field researchers are not blinded to group allocation. A blinded statistician not involved in the trial process will be responsible for the final analysis.

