In the second part of the intervention the patients' individual information need on particular topics will be determined and further addressed. In addition, the patient will be given the opportunity to receive information on other topics.

Following preliminary studies, a length of about 10 minutes is scheduled for the intervention [14]. A second intervention time will not explicitly be ruled out if the patient's information need could not be met with due to exhaustion, failing concentration or an interruption for other reasons.

The control patients will be offered a semi-structured, non-specific conversation with a member of the study group. This conversation with the patient will also take about 10 minutes. Priority will be given to topics such as mental state, experienced pain, sleeping habits and experienced anxiety.

Accompanying close relatives or friends can stay during the (control-) intervention if the participant agrees. As this can enhance the message, this will be documented in the case report form.

Before the experimental and control intervention the patients' level of consciousness and concentration will be recorded using the Richmond Agitation and Sedation Scale - RASS [24] and the Confusion Assessment Method for the ICU - CAM-ICU [25,26]. The interventions will only be carried out at RASS values ≥ -3 and a negative test outcome of the four CAM-ICU criteria. In case of lower values the patient will be re-assessed at a later date (→ 24 h interval).

The study procedure will be carried out in each center by one of the study members who are not involved in the standard care in order to receive information on the efficacy. The comparability of the intervention taking place over the different centers is guaranteed by preliminary instructions of the study personnel for the implementation of the information program and the control intervention. Additionally, the coordinating center in Marburg will centrally monitor the whole trial.

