#### Secondary Outcomes

In addition to the anxiety-related part of the CINT questionnaire a Visual Analogue Scale-Anxiety - VAS-A [27] supported by the Faces Anxiety Scale [28] is used. Evaluation of potential discrepancies between the retrospectively reported anxiety and the measured anxiety during the ICU-stay is of particular interest. The State and Trait Anxiety Inventory - STAI [29] as a further anxiety-related instrument will be recorded to compare anxiety after ICU-stay.

Furthermore the CINT questionnaire [20,22] measures additional parameters of the ICU related experiences.

As a secondary variable, the patients' level of consciousness and concentration regarding a potential ICU-caused state of confusion will be surveyed with the Confusion Assessment Method for the ICU - CAM-ICU [25,26]. The test procedure CAM-ICU, also appropriate for ventilated patients, comprehends cognitive as well as process-related components. These components are illustrated using the Richmond Agitation and Sedation Scale - RASS [24] and the four delirium main criteria "acute onset", "inattention", "disorganized thinking" and "altered level of consciousness".

For the analysis of additional effects the duration of stays (ICU, intermediate care, standard ward, hospital) and routine date on the course of inpatient treatment are recorded. Socio-demographic data like age, gender, marital status and routine treatment data like medical diagnoses will be documented thoroughly.

Uncertainty tolerance will be measured using the Uncertainty Tolerance Scale [30] and semi-structured questions on convalescence are asked to get a qualitative impression of the participants health state.

Expected results will contribute to an improved communication in the ICU and finally to an improved quality of life as a desired treatment goal [31-33]. Therefore we will measure quality of life using the Schedule for Evaluation of Individual Quality of Life - SEIQoL [34], and the SF-12 [35]. For this reason we implemented a paper questionnaire version of the SEIQoL to test for acceptance of a self evaluation form for this kind of quality of life questionnaire.

All measurements and the timeline are summarized in Table 2.

**Table 2 T2:** Measurements.

t_0_	day of recruitment (ICU)	▪ Socio-demographic data, routine treatment data^2^ ▪ Acute ICU-Syndrome (CAM-ICU incl. RASS)^2^ ▪ Anxiety (VAS-A)^1^
t_1_	24 h after study intervention	▪ Acute ICU-Syndrome (CAM-ICU incl. RASS)^2^ ▪ Anxiety (VAS-A)^1^

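### Allocation is tied to inclusion, not to passing the RASS/CAM-ICU check, so patients can be randomised before it is known that they can receive either conversation

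*Protocol article*

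**What the plan says.** All references are to the protocol article.

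- **Randomization:** allocation is stratified by center and unit and is concealed by "opaque, consecutively numbered envelopes after the inclusion of the study patients". No moment is fixed relative to ICU admission, the t0 measures or the readiness check.
- **Inclusion and exclusion criteria:** no RASS or CAM-ICU condition is listed. Impaired cognition or judgment is an exclusion, as is sharing a room with another trial patient.
- **Recruitment of participants:** elective patients "will be informed about the possibility of taking part in the trial before the transfer to the ICU or before the surgery", and consent is taken then. All others "will be informed about the trial in the early stages of their intensive care stay and will be asked to take part". Where a custodian is appointed, the custodian is asked.
- **Study procedure:** "The interventions will only be carried out at RASS values ≥ -3 and a negative test outcome of the four CAM-ICU criteria". For patients who fall short, "In case of lower values the patient will be re-assessed at a later date", at a 24 h interval. No limit on attempts is given, and no rule for a patient who never passes. One study member per center carries out the procedure.
- **Blinding:** "Patients and field researchers are not blinded to group allocation".
- **Table 2:** t0 is the recruitment day, located in the ICU, with CAM-ICU/RASS and a self-rated VAS-A. t1 and t2 fall 24 h and 48 h after the study intervention. The primary outcome is taken at t3, on admission to the standard ward.
- **Data analysis:** all outcomes follow intention-to-treat.

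**The concern.** Inclusion and readiness for the conversation are separate steps, and allocation is attached to the first. Three things are at stake.

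1. **Untreated randomised patients.** Anyone allocated before the check may not pass it in time. Under intention-to-treat that patient stays in the comparison and either dilutes the effect or has no primary outcome. The t1 and t2 measurements have no defined date, because they are counted from a conversation that did not happen.
2. **Baseline.** If the envelope is opened before t0 is complete, the VAS-A, a self-rating by an unblinded patient, can be given with the arm already known.
3. **Readiness decisions.** Concealment protects the decision to include. It does not protect a later decision, by unblinded staff, about when to assess and whether the patient is ready.

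**Working it through.** **Order of events.** The check is not an inclusion criterion: it is absent from the eligibility list, and patients who fall short are seen again, not excluded. So even if every patient is recruited in the ICU, the sequence of inclusion, envelope, failed check and a wait of 24 h or more is allowed as written. The opposite sequence, with the envelope sealed until the check is passed, is also compatible with the text but is not required by it.

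**The plan's own sample size.** Inputs from Sample size calculation: SD 17.0, Δ 8.50, α 0.05, β 0.20. Two-sided α is assumed, as sidedness is not stated.

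- Normal approximation: n = 2 × (1.960 + 0.842)² × (17/8.5)² = 2 × 7.85 × 4 ≈ 62.8, so 63 per group. The exact t-test gives 64.
- The stated 70 is slightly higher and therefore on the safe side. Its t-test power is 83.6%.
- The step to 100 corresponds to a 30% drop-out allowance: 70/(1 − 0.30) = 100.

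**Effect of untreated patients who do have the primary outcome.** The article gives no rate, so let u be an assumed untreated share of the analysed patients. Assume no effect in the untreated, no effect of the control conversation on the outcome, and an unchanged SD of 17. The expected difference is then 8.5 × (1 − u). Power comes from the two-sided t-test with noncentrality [8.5(1 − u)/17] × √(n/2) and 2n − 2 degrees of freedom.

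| u (assumed) | Expected difference | Power, 70 analysed per group | Power, 100 analysed per group |
|---|---|---|---|
| 0% | 8.50 | 83.6% | 94.0% |
| 5% | 8.08 | 79.7% | 91.7% |
| 10% | 7.65 | 75.3% | 88.6% |
| 20% | 6.80 | 65.2% | 80.4% |
| 30% | 5.95 | 53.8% | 69.2% |

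For example, at u = 10% and n = 70 the noncentrality is 0.45 × √35 = 2.66. With 70 analysed, about 5% untreated uses up the margin over 80%. With 100 analysed, about 20% can be absorbed.

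**Effect of untreated patients who lack the primary outcome.** A patient who dies or never reaches the standard ward contributes no value, so the mean difference is not diluted and the loss is one of numbers. If there is no other loss, 10%, 20% or 30% leave 90, 80 or 70 per group at the full 8.5 points, with power 91.6%, 88.2% and 83.6%. These patients draw on the drop-out allowance.

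**Readiness bias.** Nothing in the article allows its size or direction to be computed.

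**The case against.** A reader might infer that elective patients are randomised before surgery, because their consent is taken then. The article does not support that. The envelope comes after inclusion, and inclusion is nowhere equated with consent. Table 2 places the recruitment day in the ICU. The rule against two trial patients in one room can be settled only once a room is occupied. Pre-surgical opening is therefore an inference and forms no part of this point.

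A reader might also take untreated randomised patients as a fact, or the lower power column as the expected result. Neither follows. Untreated patients are a possibility, with no stated rate. The column for 70 presumes that the full 30% allowance has already been lost for other reasons.

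Further points carry weight. The exclusion for impaired cognition, and written consent during the ICU stay, should remove many patients who could not pass. RASS and CAM-ICU are structured, the threshold is the same in both arms, and the control conversation is meant to match the intervention in timing and length. The article does not say that the person rating readiness has seen the allocation. These limit the problem but do not remove it: consent can come through a custodian, elective consent precedes any ICU assessment, and the moment of assessment remains partly the study member's choice.

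Lastly, the moment of opening an envelope may be thought a detail for the full protocol. But the article does state an anchor, and that anchor permits allocation before the check. An analysis plan cannot repair this after the event.

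**Conclusion.** The point stands as a weakness in a stated conduct rule: as written, allocation may precede the readiness check. It should be corrected, but it is not a demonstrated bias.

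On assumed untreated shares of 10% and 20% among analysed patients, power is 75% and 65% with 70 analysed per group, and 89% and 80% with 100. Which column applies depends on how much of the drop-out allowance is spent elsewhere. To the extent that untreated patients also lack the ward-admission outcome, the loss is smaller than dilution suggests. The figures rest on two-sided α of 0.05, SD 17, no effect in untreated patients and no effect of the control conversation on the outcome.

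The gap in t1 and t2 for never-treated patients, and the exposure of t0 and readiness judgments to knowledge of the arm, follow from the permitted order of events and do not depend on these assumptions. How often they would occur is unknown.

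**What to change.** Leave consent where it is and leave the RASS/CAM-ICU check unchanged. Add to Randomization that the next envelope in the center/unit stratum is opened only after the t0 measures are recorded and the existing check is passed, immediately before the conversation. Count the 200 patients from that point, and report those who consented but never became ready in the flow chart.

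This largely removes never-treated patients from the randomised set, gives nearly every randomised patient a defined t1 and t2, and keeps t0 and the readiness judgment free of knowledge of the arm.

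The cost is one change to the envelope procedure and somewhat more consents to reach 200 randomised. The trial population is then limited to patients who become communicable, who are also the only ones to whom the program can be delivered.

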### Blinding

Patients and field researchers are not blinded to group allocation. A blinded statistician not involved in the trial process will be responsible for the final analysis.

### Study procedure

The experimental intervention is planned as a conversation with ICU-specific information on the ICU during the first stage of the ICU stay. The control intervention is planned as a non-specific conversation of the same duration and at the same point of time as the experimental intervention.

During the information intervention a standardized and an individualized part are combined: a guided conversation corresponding to the individual choice in the dialogue. Thereby patients will be given sensory and procedural information (e.g. sources of noise in the ICU, chronology) as well as coping information (e.g.: What can you do if you are feeling strained?).

The first, standardized part of the intervention comprises information on nine topics, that have been identified in preliminary studies [22,23] as relevant for patients in ICUs. The topics of the standardized part of the information program are described in Table 1.

**Table 1 T1:** Information intervention.

**Nr.**	**Topic**	**Details**
**1**	**People in the ICU**	• Health care professionals (nurses and intensive care nurses) • Attending physician • Clothing incl. specifics such as masks, gloves etc. • Change of shifts • Ward rounds

**2**	**Devices and monitoring**	• Monitor incl. central monitoring • Ventilator • Infusion and syringe pump (infusomat and perfusor) • Alarms

**3**	**Room furnishing**	• Clock • Bell system • Room size

**4**	**Individual safety**	• Tubes, drainages, wounds, urinary catheters, fixation • Tube, respiratory mask • Waking phase • Intravenous access • Bedding • Dimming of the light

**5**	**Schedule**	• Hospital stay duration • Transfer to IMC • Differences between IMC and ICU • Nutrition

**6**	**Communication**	• Nod, shake of the head • Pens

**7**	**Staff duties**	• Aspiration • Mobilization • Radiologic examinations • Personal hygiene/oral hygiene

**8**	**Conveniences**	• Analgesics and soporifics (pain relievers and sleeping pills) • Visiting hours • Information before nursing-medical interventions

**9**	**Helpful thoughts**	• Everything is done for me. That is sign that everything worked alright. • I don't have to suffer any pain; if necessary I will receive additional medication. In the meantime I can relax and continue to breathe calmly. • Only a little longer, then I have made it.

Topics of the information program.

In the second part of the intervention the patients' individual information need on particular topics will be determined and further addressed. In addition, the patient will be given the opportunity to receive information on other topics.

Following preliminary studies, a length of about 10 minutes is scheduled for the intervention [14]. A second intervention time will not explicitly be ruled out if the patient's information need could not be met with due to exhaustion, failing concentration or an interruption for other reasons.

The control patients will be offered a semi-structured, non-specific conversation with a member of the study group. This conversation with the patient will also take about 10 minutes. Priority will be given to topics such as mental state, experienced pain, sleeping habits and experienced anxiety.

Accompanying close relatives or friends can stay during the (control-) intervention if the participant agrees. As this can enhance the message, this will be documented in the case report form.

Before the experimental and control intervention the patients' level of consciousness and concentration will be recorded using the Richmond Agitation and Sedation Scale - RASS [24] and the Confusion Assessment Method for the ICU - CAM-ICU [25,26]. The interventions will only be carried out at RASS values ≥ -3 and a negative test outcome of the four CAM-ICU criteria. In case of lower values the patient will be re-assessed at a later date (→ 24 h interval).

The study procedure will be carried out in each center by one of the study members who are not involved in the standard care in order to receive information on the efficacy. The comparability of the intervention taking place over the different centers is guaranteed by preliminary instructions of the study personnel for the implementation of the information program and the control intervention. Additionally, the coordinating center in Marburg will centrally monitor the whole trial.

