t_2_	48 h after study intervention	▪ Acute ICU-Syndrome (CAM-ICU incl. RASS)^2^ ▪ Anxiety (VAS-A)^1^

t_3_	admission to standard ward	▪ Experience and emotional state in the ICU (CINT-FB)^1^ ▪ Anxiety (VAS-A)^1^ ▪ State-Anxiety (STAI-State)^1^ Estimated time for the questionnaire: 20 minutes

t_4_	discharge from hospital	▪ In-patient history and postoperative complications^2^ ▪ Length of stay and mode of discharge^2^

t_5_	3 months after discharge (by mail)	▪ Individual quality of life (SEIQoL)^1^ ▪ Quality of life (SF - 12)^1^ ▪ Uncertainty (Uncertainty Tolerance Scale)^1^ ▪ Convalescence (Semi-structured questions)^1^ ▪ Trait-Anxiety (STAI-Trait)^1^ Estimated time for the questionnaire: 15 minutes

Points of measurement and outcome measures according to case report form.

^1^Self evaluation; ^2 ^Third-party evaluation

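### The control conversation is declared equal in duration and timing, but a second session is provided for on a trigger that only the information arm can meet

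*Protocol article*

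**What the plan says.** All the relevant rules stand in the protocol article under Methods, Study procedure.

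- **Parity of the arms:** "The control intervention is planned as a non-specific conversation of the same duration and at the same point of time as the experimental intervention".
- **Information arm, length:** "a length of about 10 minutes is scheduled for the intervention".
- **Information arm, repeat:** "A second intervention time will not explicitly be ruled out if the patient's information need could not be met with", with the reasons listed as "due to exhaustion, failing concentration or an interruption for other reasons". No limit on the length, timing or number of such sessions is given.
- **Control arm, length:** "This conversation with the patient will also take about 10 minutes". Nothing is said about what happens if it is broken off.

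Other sections give the context. Randomization calls the control a sham comparator. Blinding states that neither patients nor field researchers are blinded. Primary Outcome places the anxiety score at admission to the standard ward. Table 2 sets the two intermediate measurements at "24 h after study intervention" and "48 h after study intervention".

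**The concern.** A sham conversation is there to hold attention constant, so that a difference between arms can be credited to what was said. That works only if both arms get comparable contact. Here parity is promised, and then an exception is written for one arm, on a trigger (an unmet need for information) that a patient in the other arm cannot meet.

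Exhaustion, lapses of concentration and interruptions will occur in both arms. If an information patient is visited again and a control patient in the same state is not, contact differs along with content. The primary score includes items such as loneliness, strain, uncertainty and confidence, which a further bedside visit by a study member could plausibly move. The staff who decide on a further visit know the allocation. The planned intention-to-treat ANCOVA compares the arms as randomised and cannot separate contact from content afterwards.

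**Working it through.** The plan gives no figure on this point, so the check is to set the provisions side by side and follow them for the same kind of patient in each arm.

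**1. Conversation completed at the first attempt.** Both arms have one contact of about 10 minutes. Parity holds.

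**2. Conversation broken off after m minutes (m < 10) through exhaustion, poor concentration or interruption.**

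| | Information arm | Control arm |
|---|---|---|
| Second session provided for? | Yes, if the information need is unmet | Not mentioned |
| Number of contacts, as written | 2 | 1 |
| Time of last contact | Later than planned | As planned |
| Total minutes, if the second session only completes the first | m + (10 − m) = about 10 | m |
| Total minutes, if the second session is a full one of about 10 (assumption; its length is not stated) | m + 10 | m |

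The number and timing of contacts differ on either reading of the second session. Whether total minutes exceed the planned 10 depends on that reading. Even if the second session only completes the first, an interrupted control patient who is not revisited ends with fewer minutes (m) than an interrupted information patient (about 10).

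**3. Effect on the group comparison.** Let s be the share of information patients who get a second session, and c the change in the anxiety score due to that contact alone, apart from content. The part of the mean difference due to contact is then

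s × c.

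The documents give neither s nor c, so no number can be put to the product. It tends to zero as s does, and an option that is merely left open may be used seldom. If contact lowers anxiety (assumption), the contribution favours the information arm.

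**4. The measurement clock.** The intermediate measurements are timed from the study intervention. For a patient with two sessions this can be read as the first or the last. If it is the first, the measurement times do not move. If it is the last, they move later for those patients. The article does not say which. The primary score is taken at ward admission and does not depend on this clock.

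**The case against.** The strongest case on the other side has four parts.

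- **That the second session is confined to one arm is inferred.** Nothing forbids resuming an interrupted control conversation. Study personnel are instructed in both conversations, and the Quality assessment section says that procedures were jointly developed and documented. Those documents are not shown. This stands as a limit on the wording: the article does not exclude a second control contact. It does not remove the point, because the article states the repeat rule for one arm, ties it to an information need, and says nothing for the other.
- **The second session may only finish the first.** A reader might infer that information patients receive surplus attention. The documents do not establish this, since total time may stay at about 10 minutes. The objection stands for minutes beyond 10, but not for the number and timing of contacts.
- **The t1 and t2 measurements.** A reader might infer that these are shifted, and so biased, in one arm. The documents do not support that. A shift arises only if the last session starts the clock. Table 2 follows a case report form that is not shown and may settle the matter. The measures concerned (VAS-A and CAM-ICU with RASS) are secondary, and their analyses are declared exploratory. The 24-hour interval in Study procedure concerns re-assessing consciousness before the conversation, not a gap between sessions.
- **The randomised comparison is still valid** as a comparison of the two packages as delivered. That is correct. What is weakened is the attribution of a difference to information, which is the mechanism named under Trial objective.

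**Conclusion.** The point holds in a limited form. The declared equality of duration and timing and the second-session provision do not fit together, because no equivalent is stated for a control conversation cut short for the same reasons. Followed as written, the number and timing of contacts can differ between arms, and total minutes may differ too. Part of an observed difference could therefore be due to contact.

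The size cannot be derived from the documents and is small if second sessions are rare. The conclusion assumes that interrupted control conversations are not resumed, which the article neither says nor rules out. It does not extend to a claim of proven surplus attention, a numerical bias in the primary result, or biased t1 and t2 measurements. It is worth correcting before recruitment because the trial is unblinded, the sham exists to equalise contact, and contact that goes unrecorded cannot be reliably reconstructed later.

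**What to change.** 1. Reconcile the parity statement and the second-session provision in Study procedure, so that one rule on resuming or repeating a conversation applies in both arms. Word its triggers so that a patient in either arm can meet them. Which rule is chosen is for the sponsor.
2. Record the number and minutes of contacts for every patient in both arms, if the case report form does not already do so. The article already provides for documenting the presence of relatives. These data would allow contact to be reported by arm.
3. As an optional clarification, state one time zero for t1 and t2 that is the same in both arms. The first or the completed conversation could each be defended.

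**Cost:** a change of protocol wording, submitted to the ethics committees as an amendment as the article foresees, and two fields in the case report form. Depending on the rule chosen, there may be a few short extra control contacts by the same study member.
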